## Abstract

**Introduction:**

Patients with malignant pleural mesothelioma (MPM) may develop painful ‘procedure tract metastasis’ (PTM) at the site of previous pleural interventions. Prophylactic radiotherapy has been used to minimise this complication; however, three small randomised trials have shown conflicting results regarding its effectiveness. The surgical and large bore procedures in malignant pleural mesothelioma and radiotherapy trial (SMART Trial) is a suitably powered, multicentre, randomised controlled trial, designed to evaluate the efficacy of prophylactic radiotherapy within 42 days of pleural instrumentation in preventing the development of PTM in MPM.

**Methods and analysis:**

203 patients with a histocytologically proven diagnosis of MPM, who have undergone a large bore pleural intervention (thoracic surgery, large bore chest drain, indwelling pleural catheter or local anaesthetic thoracoscopy) in the previous 35 days, will be recruited from UK hospitals. Patients will be randomised (1:1) to receive immediate radiotherapy (21 Gy in 3 fractions over 3 working days within 42 days of the pleural intervention) or deferred radiotherapy (21 Gy in 3 fractions over 3 working days given if a PTM develops). Patients will be followed up for 12 months. The primary outcome measure is the rate of PTM until death or 12 months (whichever is sooner), as defined by the presence of a clinically palpable nodule of at least 1 cm diameter felt within 7 cm of the margins of the procedure site as confirmed by two assessors. Secondary outcome measures include chest pain, quality of life, analgaesic requirements, healthcare utilisation and safety (including radiotherapy toxicity).

**Ethics and dissemination:**

The trial has received ethical approval from the Southampton B Research Ethics Committee (11/SC/0408). There is a Trial Steering Committee, including independent members and a patient and public representative. The trial results will be published in a peer-reviewed journal and presented at international conferences.

**Trial registration number:**

ISRCTN72767336.

Strengths and limitations of this studySuitably powered multicentre, randomised controlled trial of prophylactic radiotherapy in malignant pleural mesothelioma.Robust 1 year patient follow-up.All large bore pleural interventions are eligible, including indwelling pleural catheters.Small bore chest tubes excluded.

## Introduction

Malignant pleural mesothelioma (MPM) is an aggressive tumour, which is universally fatal. In 2012, there were 2535 mesothelioma deaths in the UK alone and the incidence is predicted to increase.^1^
^2^ In order to obtain a robust histological diagnosis and to manage symptomatic pleural effusions, patients commonly undergo a number of diagnostic and therapeutic pleural interventions during the disease course.^3^
^4^

As a complication of iatrogenic instrumentation of the pleural cavity, tumour can spread to the site of previous interventions, resulting in procedure tract metastases (PTMs), which can be intensely painful.

Mesothelioma is sensitive to radiation therapy in vitro,^5^ but its use as a radical treatment is limited by unacceptable toxicity. However, prophylactic radiotherapy to pleural intervention sites can be given with minimal side effects and a small randomised controlled trial (RCT) was performed in 1995 by Boutin and colleagues to evaluate its efficacy. None of the 20 patients randomised to receive prophylactic radiotherapy (21 Gy in 3 fractions over 3 days within 15 days of the procedure) developed a PTM, but 8 of the 20 patients (40%) in the untreated arm did.^6^

Based on this small study, prophylactic radiotherapy to procedure tracts in mesothelioma became accepted practice worldwide.^4^
^7–9^ However, the very high rate of PTM in the control arm of the Boutin study was felt to be more than that seen in routine clinical practice, particularly for patients undergoing small bore pleural procedures such as image-guided biopsies or simple pleural fluid aspirations.^10–12^ Additionally, as prophylactic radiotherapy can be burdensome for patients so soon after their diagnosis (requiring up to 4 hospital attendances) and may be associated with some side effects, it was felt further evidence should be obtained to validate its routine clinical use.

Two further RCTs were therefore undertaken; the results of which called into question what had become routine clinical practice.^13^
^14^ Bydder *et al*^13^ randomised 43 patients with MPM (who had undergone 58 recent small and large bore pleural procedures) to receive a smaller dose of prophylactic radiotherapy (10 Gy in 1 fraction) or no radiotherapy. No significant difference in the occurrence of PTM was identified (7% in the radiotherapy arm vs 10% in the control arm).

These findings were mimicked in another small UK-based RCT evaluating 21 Gy in three fractions of radiotherapy given over 3 days within 21 days of the pleural intervention. Of 61 patients recruited, 7 patients (23%) developed a PTM in the radiotherapy arm, compared with 3 patients (10%) in the control arm.

These conflicting trial results have led to clinical equipoise regarding the benefits of prophylactic radiotherapy and calls from the mesothelioma community for a suitably powered RCT to conclusively establish its role.^15^ In a recent UK survey, 75% of responding centres offered prophylactic radiotherapy, but treatment protocols and patient selection varied greatly between institutions.^15^ Additionally, the advent of chemotherapy for mesothelioma^16^ and the increasing use of indwelling pleural catheters (IPCs) for management of malignant pleural effusion in mesothelioma has resulted in uncertainty regarding the use of prophylactic radiotherapy in these contexts.^17^
^18^ This study was designed to specifically address these questions with a suitably powered, randomised, controlled trial.

## Methods and analysis

The surgical and large bore procedures in malignant pleural mesothelioma and radiotherapy trial (SMART Trial) is a multicentre, prospective, RCT. The trial is sponsored by North Bristol NHS Trust and coordinated by The Respiratory Research Unit at North Bristol NHS Trust. Data management is undertaken by the Oxford Respiratory Trials Unit. The trial is registered on the International Standardised Randomised Controlled Trial Registry (ISRCTN72767336) and funded by the National Institute for Health Research (NIHR), Research for Patient Benefit (RfPB) Programme. The study is included in the NIHR Clinical Research Network portfolio (ID: 11023). The trial will be conducted in accordance with the Declaration of Helsinki and Good Clinical Practice (GCP).

The primary research question is to evaluate whether prophylactic radiotherapy prevents PTM following large bore pleural procedure in MPM.

The secondary research questions are:

In MPM:
Does prophylactic radiotherapy lead to differences in patient symptoms and quality of life indices as compared to radiotherapy given in the event a PTM develops?What proportion of PTM are symptomatic (ie, painful) and to what extent is this modulated by giving prophylactic radiotherapy?In a subgroup of patients with IPCs, is prophylactic radiotherapy effective in reducing PTM?Does prophylactic radiotherapy cause toxicity and impact on the quality of life of patients?Is deferred radiotherapy (given when a nodule develops) as effective as prophylactic radiotherapy at controlling symptoms?What is the patient experience of immediate and deferred radiotherapy?What are the health economic implications of giving prophylactic radiotherapy as compared to deferred radiotherapy in this patient group?

### Setting

Two hundred and three patients with a histocytologically proven diagnosis of MPM, who have undergone a large bore pleural intervention in the preceding 35 days, will be recruited from UK hospitals (see online supplementary appendix 1 for details of recruiting centres). Patients will be randomised to receive either immediate radiotherapy (within 35 days of their pleural intervention) or deferred radiotherapy (in the event that the patient develops a PTM) and followed up until death or a year (whichever is sooner). The study flow diagram is shown in figure 1.

**Figure 1 BMJOPEN2014006673F1:**
[figure not shown]
Trial overview flow diagram (MDT, multidisciplinary team; VATS, video-assisted thoracoscopic surgery).

### Participant screening and selection

All patients discussed at the regional mesothelioma multidisciplinary team (MDT) meetings will be identified as potential trial candidates. Consecutive, eligible patients will be invited to participate and will be provided with a patient information sheet (PIS; see online supplementary appendix 2). Patients can only be enrolled into the SMART Trial once.

### Inclusion criteria

A histocytologically proven diagnosis of mesothelioma, as confirmed by a MDT meeting.One of the following pleural interventions in the past 35 days:
Open pleural biopsy;Surgical thoracotomy or video-assisted thoracoscopic surgery (VATS);Local anaesthetic thoracoscopy;Large bore chest tube insertion (greater or equal to 20 Fr inserted by either a seldinger technique or blunt dissection);IPC insertion.Written informed consent.

### Exclusion criteria

Age <18 years;Expected survival <4 months;Pregnancy or lactation;Inability to give informed consent or comply with the protocol;Previous radiotherapy which would result in an unacceptable overlap with the proposed treatment field;The patient does not have access to a telephone;A clinically palpable nodule of at least 1 cm diameter felt within 7 cm of the margins of the procedure site at the initial trial visit.

### Informed consent

A doctor will confirm patient eligibility prior to consent being taken. Patients will be given at least 24 h to consider the PIS and time to ask questions prior to written informed consent being taken by a trial doctor, nurse or radiographer. The consent form can be viewed in online supplementary appendix 3.

### Randomisation

Following informed consent, patients will be randomly assigned (1:1) to receive either immediate prophylactic radiotherapy (within 42 days of the pleural intervention) or deferred radiotherapy (given if the patient develops a PTM).

Treatment allocation will be performed over the telephone by UKCRC Oxford Respiratory Trials Unit. The randomisation sequence will be generated using a validated, online randomisation service (Sealed Envelope, London, UK; http://www.sealedenvelope.com). Minimisation with a random component will be used to reduce the baseline between-group differences.

The minimisation factors are:
Histological tissue type of mesothelioma (epithelioid only or other);IPC or other pleural procedure;Surgical procedure (ie, open pleural biopsy, thoracotomy or VATS) or non-surgical procedure.

Patients and clinicians will not be blinded to treatment allocation; however, the data analysis will be conducted in a blinded fashion.

### Standard care

All patients will be discussed in an MDT meeting. If appropriate, patients will be referred to the local oncologist for discussion and consideration of their treatment options. Aside from prophylactic radiotherapy, other treatments offered to patients will be guided by clinical need and are at the discretion of the patient's clinicians.

Ongoing clinical review will either take place in oncology or respiratory clinic. Patients requiring assistance from other services, for example, the surgeons, palliative care team or hospice, will be referred when needed by the clinical team. Patients who require radiotherapy for another indication (other than prophylactic radiotherapy as part of the trial or for treatment of a PTM) can be treated at the discretion of the local oncologist.

Co-enrolment in other clinical trials will be discussed on an individual basis, but will only be considered if compliance with both protocols can be ensured. Patients can withdraw from the trial at any time without their clinical care being affected.

### Interventions

The full trial-specific procedure for radiotherapy can be found in online supplementary appendix 4.

#### Immediate radiotherapy

For patients in the immediate (prophylactic) radiotherapy arm, radiotherapy should be given within 35 days of the pleural procedure for which the patient has been randomised. Under exceptional circumstances, the first fraction may be postponed for up to 42 days but a reason must be clearly stated.

The treatment to be given will be 21 Gy in three fractions over 3 working days. The preferred procedure is to treat the patient using electrons of appropriate energy to treat the chest wall to at least 90% (using bolus if necessary). Alternatively, kilovoltage (kV) photons (minimum 220 kV) can be used if the depth dose to the chest wall is adequate. Megavoltage photons (MV) can be used if clinically indicated. A single direct beam will be used in the majority of cases.

The volume to be treated must be acceptable to the treating clinical oncologist and the treatment area should be no less than 7 cm in any one direction.

For pleural procedures other than IPCs:
Suggested clinical target volume (CTV): chest drain and surgical sites/scars with at least a 3 cm margin;Suggested planning target volume (PTV): CTV+0.5 cm if using kV photons or CTV+1 cm if using electrons;The total radiotherapy field will be equivalent to the PTV.

For patients with an IPC in situ:
Suggested CTV: pleural puncture site, the whole of the catheter tract and the skin exit site with at least a 3 cm margin;Suggested PTV: CTV+0.5 cm if using kV photons or CTV+1 cm if using electrons;The total radiotherapy field will be equivalent to the PTV.

If patients in the immediate radiotherapy arm develop a PTM, further radiotherapy treatment to the site is at the discretion of the treating oncologist. Details of the relationship of the PTM to the prophylactic radiotherapy field will be recorded.

#### Deferred radiotherapy

If patients in the deferred radiotherapy arm are diagnosed with a PTM, 21 Gy in three fractions of radiotherapy will be given within 35 days of the PTM being diagnosed. The dose, technique, energy and beam arrangement will be the same as for the immediate radiotherapy arm and the treatment volume must be acceptable to the treating clinical oncologist.
Suggested CTV: palpable nodule with at least a 2 cm margin;Suggested PTV: CTV+0.5 cm if using kV photons or CTV+1 cm if using electrons;The total radiotherapy field will be equivalent to the PTV.

### Data collection and management

#### Randomisation visit

Clinical data will be collected at the randomisation visit. This will include a history and chest wall examination and patients will be asked to complete two quality of life questionnaires (EQ5D and QLQ-C30) and visual analogue scale (VAS) scores to quantify their current degree of chest pain.

#### Follow-up visits

Follow-up visits will be undertaken at 1, 3, 6, 9 and 12 months postrandomisation. These will include a focused history (including details of radiotherapy toxicity, mesothelioma treatments received, analgaesia use and healthcare utilisation) and a chest wall examination to identify PTMs and radiation toxicity. The patient will also be invited to complete quality of life questionnaires (QLQ-C30 and EQ5D), a VAS score for chest pain and patient experience questionnaires regarding radiotherapy or the development of a PTM (if applicable).

#### Telephone follow-up

When patients are not seen in clinic, they will receive a monthly phone call from a research nurse to enquire about symptoms at the intervention site. They will also be invited to complete a chest pain VAS score, which will be returned by post. Should they develop problems at the intervention site, a clinic appointment will be arranged as soon as possible (ideally within 10 days).

#### Semistructured interviews

A small, qualitative substudy will explore patients’ experiences of being in the trial, their perceptions of the treatments and risks involved, to inform the trial results. Participants at the Bristol and Oxford sites will be invited to take part in semistructured qualitative interviews by a research nurse approximately 6 months after randomisation (see online supplementary appendix 5 for interview schedule).

From those who agree to be interviewed, a purposive maximum variation sample will be selected of up to 20 patients. Patients from Bristol and Oxford who develop a tract metastasis at any point after their 6-month follow-up visit will be invited to undertake a follow-up interview.

The data will be analysed using a thematic approach and the themes produced will help to describe participants’ views of the trial and how treatment can be optimised for these patients. This will be published separately to the main trial outcomes.

#### Data management

Clinical Record Forms will be completed by the trial team at the recruiting centre and sent to the Oxford Respiratory Trials Unit. Data will then be entered onto the trial database (OpenClinica clinical trials software). Missing data and data queries will be highlighted to the trial teams on a monthly basis. The Clinical Record Forms will only identify patients using their personal trial identification number (no identifiable patient information).

### Primary outcome

The primary outcome will be the difference in the incidence of development of PTM within 7 cm of the site of pleural intervention within 12 months from randomisation between the study arms.

A PTM will be defined as a clinically palpable nodule of at least 1 cm diameter felt within 7 cm of the margins of the procedure site as confirmed by two assessors. One of the assessors must be a doctor who feels that clinically the nodule is a tract metastasis. The assessors will be doctors, nurses or radiographers who have read the chest wall examination standard operating procedure (SOP) (see online supplementary appendix 6) and feel confident to undertake the examination. In the event of disagreement between the assessors, they will examine the patient together to reach a consensus.

The presence or absence of PTM within 12 months of randomisation will be compared using Fisher's exact test. This was chosen in preference to ‘time-to-event’ analysis for the primary outcome analysis, as prophylactic radiotherapy is not likely to change the speed with which the events occur, but rather prevent them from occurring, thereby violating the necessary assumptions of survival models. Time-to-event data will be modelled using regression analysis, but this will form part of the secondary analysis.

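### The primary endpoint includes a doctor's opinion given by assessors who may both know the arm; thresholds and a second assessor limit the resulting bias but do not remove it

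*Protocol article*

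**What the plan says.** The Primary outcome section of the protocol article gives this definition of a procedure tract metastasis (PTM): "clinically palpable nodule of at least 1 cm diameter felt within 7 cm of the margins of the procedure site as confirmed by two assessors". It then adds an opinion: "One of the assessors must be a doctor who feels that clinically the nodule is a tract metastasis". Assessors may be doctors, nurses or radiographers who have read the chest wall examination procedure and feel confident to carry it out. If the two differ, "In the event of disagreement between the assessors, they will examine the patient together to reach a consensus".

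On masking, the Randomisation section says: "Patients and clinicians will not be blinded to treatment allocation; however, the data analysis will be conducted in a blinded fashion".

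The label has different consequences in the two arms. Under Deferred radiotherapy, "If patients in the deferred radiotherapy arm are diagnosed with a PTM, 21 Gy in three fractions of radiotherapy will be given". Under Immediate radiotherapy, further treatment of a PTM is left to the treating oncologist.

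The Follow-up visits section gives both arms the same schedule and describes "a chest wall examination to identify PTMs and radiation toxicity" at each visit.

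**The concern.** Open treatment is unavoidable in this trial, but open assessment by both readers is not. The article does not require either assessor to be independent of the patient's care or unaware of the arm. It describes no masked adjudicator and no imaging or histological confirmation. Blinding starts at the data analysis, after the label has been given.

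Three features could make the labelling depend on the arm:

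- **Opinion on cause.** A doctor who knows that the site was irradiated may put a doubtful lump down to scarring or radiation change. A doctor who knows that it was not may call it a PTM.
- **Consequence of the label.** In the deferred arm the label leads to trial radiotherapy. In the immediate arm it leads to nothing fixed.
- **Shared examination.** The visit that looks for PTMs also looks for radiation toxicity, so the examiner is pointed at signs that reveal the arm.

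A joint examination after disagreement then yields one shared reading from two people who may both know the allocation. At stake is the only primary comparison, in a trial that expects few events.

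**Working it through.** **Inputs from the article.** PTM rates of 2% (immediate) and 15% (deferred), 90% power, 5% level, 3% loss to follow-up and 203 recruited (Sample size calculation). Two-sided p values (Statistical analysis plan section). Fisher's exact test (Primary outcome).

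**The plan's own figure.** The unpooled two-proportion formula gives, per arm, (0.02×0.98 + 0.15×0.85)×(1.960 + 1.282)² / 0.13² = 91.5, so 92 per arm and 184 in total. The article states 180. With loss to follow-up, 184/0.97 = 190, against 185 stated. Both agree within 3%, so this point rests on no arithmetic error in the sample size.

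**Analysed number.** 203×0.97 = 197, or about 98 per arm. Expected events are 0.02×98 = 2 and 0.15×98 = 14.7 (taken as 15), about 17 in all.

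**How many labels matter at the design rates** (two-sided Fisher, 98 per arm):

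| Immediate v deferred | p | Reading |
|---|---|---|
| 2 v 15 | 0.0015 | as designed |
| 5 v 15 | 0.032 | three immediate-arm PTMs had been missed |
| 6 v 15 | 0.063 | four immediate-arm PTMs had been missed |
| 2 v 10 | 0.033 | five deferred-arm PTMs had been over-called |
| 2 v 9 | 0.058 | six deferred-arm PTMs had been over-called |

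If 2 v 15 were observed, significance would depend on arm-dependent error if four immediate-arm PTMs had been missed, or six deferred-arm labels were wrong.

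**False-positive rate with no true effect.** Take a true rate of 10% in both arms. The article gives no misclassification rates, so those below are assumptions. Observed immediate rate = 0.10×(1 − missed share). Observed deferred rate = 0.10 + 0.90×(over-call share among patients without PTM). The last column is the exact probability that Fisher's test rejects at 98 per arm.

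| Assumed error | Immediate | Deferred | Rejection |
|---|---|---|---|
| None | 10% | 10% | 2.8% |
| 3% over-called, deferred arm only | 10% | 0.10 + 0.90×0.03 = 12.7% | 5.9% |
| 30% missed, immediate arm only | 0.10×0.70 = 7.0% | 10% | 7.3% |
| 5% over-called, deferred arm only | 10% | 0.10 + 0.90×0.05 = 14.5% | 11.5% |
| 30% missed and 3% over-called | 7.0% | 12.7% | 19.5% |

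**The case against.** The best reply is that this is an ordinary open-label clinical endpoint with sensible safeguards. The nodule must be palpable, at least 1 cm across and within 7 cm. Two people must confirm it, one of them a doctor. All assessors work from a common procedure, both arms are examined on the same schedule, and PTM size is collected as a secondary outcome. This stands, so a reader who inferred that nothing in the endpoint limits the bias would be wrong. None of these measures removes knowledge of the arm, however, and the size of a declared PTM says nothing about a lump that was dismissed.

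Four other stronger readings are tempting, and the document does not support them:

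- **That the direction is certain.** The Introduction describes equipoise and cites a small UK trial with more PTMs after radiotherapy (23% v 10%). Closer inspection of an irradiated field could raise detection in the immediate arm.
- **That disputed or rejected nodules go unrecorded.** The article does not say. A disagreement rule presupposes two initial opinions, and the examination procedure, record forms and analysis plan are not shown.
- **That one nodule decides the trial.** This is true only on the boundary between 2 v 9 and 2 v 10. Any test with a threshold has such a pair.
- **That the false-positive rate is about 19%.** That figure combines two assumed errors acting in the same direction. Singly they give 7.3% and 5.9%.

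It is also fair to say that masking will be imperfect, because skin change can disclose the arm, and that enrolment ended in August 2014 (Trial status).

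**Conclusion.** The concern holds in a limited form. Followed exactly, the plan lets both assessors know the arm when they give an opinion that decides the primary outcome, settles their disagreements jointly, and attaches a fixed treatment consequence to the label in one arm only. Existing safeguards narrow the discretion, and blinded data analysis does not address what remains. The likely direction favours prophylactic radiotherapy, but this is a judgement and not a demonstrated fact.

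The size is moderate. At the design rates, four to six arm-dependent labels out of about 17 expected events separate a significant from a non-significant result. With no true effect and 10% in both arms, the rejection rate rises from 2.8% to between 5.9% and 11.5% for a single assumed error, and to 19.5% for the combined one. These figures illustrate sensitivity. They do not estimate the bias in this trial, because no misclassification rate is documented. The point merits correction where correction is still possible, but it does not invalidate the endpoint.

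**What to change.** For the remaining visits, and before the analysis:

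1. Where feasible, make one of the two assessors already required a colleague who is not told the allocation, and ask the patient not to disclose it.
2. Have each assessor write down a verdict, nodule size and distance before any joint examination.
3. Log every palpable nodule of at least 1 cm within 7 cm of the procedure site in both arms, including those judged not to be a PTM.
4. Pre-specify two sensitivity analyses of the primary outcome, as far as existing records permit: (a) PTM called independently by both assessors; (b) any such nodule, whatever its judged cause.

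If the examination procedure or analysis plan already provides for items 2 to 4, only item 1 is new. The primary definition and its analysis stay as they are.

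**Cost.** No additional assessor role or procedure is needed, but small sites must find a colleague who has not been told the arm, and skin change will unmask some examinations. Analysis (b) removes the opinion on cause but not differences in detection, and it will count lumps that are not metastases. Events already assessed cannot be re-read masked, so for those patients only the sensitivity analyses can help, and only where the records allow.
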